## Plans for collection, laboratory evaluation and storage of biological specimens for genetic or molecular analysis in this trial/future use {33}

In selected study sites, biological samples will be collected which will be stored for future analysis as part of a separate research programme aiming to understand biological phenotypes in the perioperative period. This work will be subject to separate ethical approval and separate funding application(s). With patient consent, 30 mL blood samples (approximately) will be taken on two occasions: at baseline (any time between consent and the beginning of the surgery) and on post-operative day 1 at 12–24 h following the end of surgery or as close as possible. This will be processed according to a specified standard operating procedure. Samples will be transferred in batches, at a time of mutual convenience, to a laboratory at Queen’s University Belfast for analysis and storage for future use. If a patient is enrolled but not randomised, sampling and data collection will proceed unless the patient is specifically withdrawn from the substudy.

## Statistical methods

### Statistical methods for primary and secondary outcomes {20a}

All randomised participants, regardless of whether they received their randomised intervention or not, will be included in all trial analyses according to their randomised allocation using all data collected up to their final follow-up in the trial (180-day time point, or their censor date if withdrawn or lost to follow-up). As the protocol states that randomisation should to be undertaken after induction of anaesthesia, where possible, withdrawal of consent prior to surgery is not anticipated, although later withdrawal from follow-up could occur and such participants will not be included in relevant denominators. Where a participant specifically requests to withdraw from follow-up, data collected up to the point of withdrawal will still be used, and permission will be sought to collect data from medical records without contacting the participant. In this way, all primary statistical analyses will be undertaken on an intention to treat basis where possible to preserve randomisation, avoid bias from exclusions and preserve statistical power.

For the primary outcome of DAH-30, appropriate point estimates and measures of variation will be reported and presented graphically for each of the two randomised arms (as determined by the distribution of the data). Randomised arms will be compared using appropriate regression techniques for count data, determined following examination of the distributions of the trial data and consideration of possible under- or over-dispersion, but anticipated to be zero-inflated Poisson regression model or zero-inflated negative binomial regression model. The model will include minimisation variables (hospital site, emergency vs elective surgery, thoracic vs abdominal surgery).

The secondary outcomes of PPC rates and mortality rates will be assessed across randomised arms using chi-squared tests, with additional logistic regression used to adjust for minimisation variables. Participant’s Quality of Recovery (QoR-15) score will be calculated using the appropriate scoring manual and reported by randomised arm using appropriate point estimates and measures of variation.

The safety outcome of allergic reaction rates and allergic sensitisation substudy findings will be presented using descriptive statistics. A comparison of the risks of different patient groups having 0, 1, 2, or 3 positive results from these tests will be explored using appropriate regression techniques for count data, determined following examination of the frequency of incidences within the trial. The incidence of positive allergy testing to sugammadex will be compared to current estimates of baseline population sensitisation to rocuronium, providing a comparator with which to understand future sensitisation rates to sugammadex.

A Consolidated Standards of Reporting Trials (CONSORT) flow diagram will illustrate the frequency of participants:Assessed for eligibility.Excluded prior to randomisation (and the frequency of each reason for exclusion).Randomised.Allocated to each randomisation arm.Receiving or not receiving their randomised treatment.Followed up at each protocol specified timepoint (and reasons for loss to follow-up).

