## Hypothesis and objectives {7}

We hypothesise that in adults aged 50 years or older, the use of sugammadex for reversal of neuromuscular blockade at the end of elective or emergency major abdominal or non-cardiac thoracic surgery will be associated with fewer PPCs, and thereby a greater number of days alive and out of hospital at 30 days compared with neostigmine.

The primary objective of SINFONIA is to determine whether sugammadex is superior to neostigmine after elective or emergency major abdominal or non-cardiac thoracic surgery in terms of days alive and out of hospital at 30 days (DAH-30).

Secondary objectives are to determine whether sugammadex is superior to neostigmine in terms of prevention of PPCs, mortality and other patient-centred outcomes after elective or emergency major abdominal or non-cardiac thoracic surgery; to determine the cost effectiveness of sugammadex compared with neostigmine; and to estimate the rate of allergic sensitisation after a single exposure to sugammadex.

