#### Crossover

Due to more rapid onset of action with sugammadex than neostigmine, and ability to reverse more profound degrees of neuromuscular blockade, the risk of crossover is greatest from neostigmine to sugammadex. Possible scenarios include the presence of deep neuromuscular blockade at the end of surgery, for example if surgery is completed more quickly than expected or a larger dose of neuromuscular blocking drug is given towards the end of the case.

Strategies to ensure eligibility and avoid crossover therefore include (a) encouraging, though not mandating, that randomisation occurs close to the timepoint when neuromuscular reversal is given, i.e. as late as possible, (b) encouraging clear communication between research delivery teams and treating anaesthetists to ensure eligibility for the trial is confirmed as close as possible to the time of randomisation, and (c) providing written guidance to anaesthetists to remind them of national guidelines supporting the routine use of quantitative neuromuscular monitoring to guide dosing of neuromuscular blocking drugs and reversal agents. These measures are intended to minimise the risk of a trial participant being randomised but not receiving a reversal agent.

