## Sample size {14}

The trial will include 2500 participants (1250 per trial arm). Based on data from the Secure Anonymised Information Linkage (SAIL) databank in Wales, we expect participants in the neostigmine arm to experience a mean DAH-30 of 22.4 days (SD 7.4). Assuming a standard deviation of 7.5, with a 5% two-sided significance level and 90% power, the randomisation of 2500 participants will allow detection of a one-day difference in DAH-30 between trial arms, whilst allowing for a 5% loss to follow up, e.g. due to withdrawal of consent or transfer to a non-participating hospital. This sample size will also allow detection of a 3% absolute difference in the incidence of PPCs between trial arms with at least 85% power and 5% two-sided significance, assuming a PPC rate of approximately 7%.

The allergic sensitisation substudy will recruit up to 250 participants, 200 of whom will have received sugammadex and 50 neostigmine. No formal sample size calculation was carried out for the substudy.

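### Read literally, the rule that every analysis follows randomised allocation also covers allergic reactions and sensitisation, which the protocol elsewhere defines by drug received

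*Protocol article*

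**What the plan says.** **The general rule.** Section {20a} of the protocol article, on primary and secondary outcomes, opens by stating that all randomised participants, "regardless of whether they received their randomised intervention or not", "will be included in all trial analyses according to their randomised allocation". The same paragraph closes in narrower terms: "all primary statistical analyses will be undertaken on an intention to treat basis where possible".

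**The allergy outcomes.** Outcomes {12} lists both the allergic-reaction safety outcome and the substudy's sensitisation rate under the secondary outcome measures. Section {20a} then says: "The safety outcome of allergic reaction rates and allergic sensitisation substudy findings will be presented using descriptive statistics". It also plans an exploratory regression, described as "A comparison of the risks of different patient groups having 0, 1, 2, or 3 positive results", without saying whether those groups are formed by allocation or by receipt.

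**Exposure-based wording elsewhere.** Hypothesis and objectives {7} sets the aim "to estimate the rate of allergic sensitisation after a single exposure to sugammadex". Sample size {14} counts the substudy's 250 participants by receipt: "200 of whom will have received sugammadex and 50 neostigmine". Outcomes {12} times the safety outcome from administration of the study drug. Trial design {8} intends to combine allergy testing with clinical hypersensitivity reactions to sugammadex seen in the trial.

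**Crossover.** The Crossover section says that "the risk of crossover is greatest from neostigmine to sugammadex". The Eligibility section under {11c} adds that some anaesthetists may give no reversal agent. The only analysis by receipt, in {20c}, is an optional per-protocol sensitivity analysis.

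**The concern.** Intention to treat is the right principle for days alive and out of hospital, pulmonary complications and mortality, because it protects the randomised comparison. An allergic reaction or a positive skin test to sugammadex is different: it is a consequence of the molecule the patient was given. If a patient allocated to neostigmine is given sugammadex and reacts, a table by allocation records that reaction under neostigmine and leaves the exposure out of the sugammadex denominator.

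This bears on one of the trial's stated purposes, which is to project the likely incidence of sugammadex hypersensitivity as UK use grows. That projection needs the people exposed to sugammadex as its denominator. The events are so rare that one misplaced case could determine how the table reads.

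**Working it through.** **1. Is there an exception in the text?**

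| Place in the protocol article | Basis |
|---|---|
| {20a}, opening rule | allocation, all analyses, receipt disregarded |
| {20a}, end of the same paragraph | intention to treat for primary analyses, where possible |
| {20a}, allergy and sensitisation | descriptive; grouping not stated |
| {7}, sensitisation objective | exposure to sugammadex |
| {8}, trial design | reactions to sugammadex |
| {12}, safety outcome | time from study drug administration |
| {14}, substudy size | drug received |
| Follow-up testing at 6 weeks to 6 months | clinical assessment depends on group allocation |
| {20c}, per-protocol option | receipt, optional; excludes patients who did not get the allocated drug and does not reassign them |

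No line says that allergy outcomes are grouped by drug received, and the widest rule says that they are not. The exposure-based lines point the other way.

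**2. The plan's own figure.** The protocol gives no figure on this point. Its sample size reproduces: n per arm = 2(1.960 + 1.282)² × 7.5² / 1² gives 1183, so 2366 in total, and 2366/0.95 = 2491 against the stated 2500. Nothing below changes it.

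**3. Share of sugammadex exposures misplaced.** Let c be the proportion of the 1250 neostigmine-allocated patients who are given sugammadex. The protocol states no value, so c is an assumption. Assume also that everyone allocated sugammadex receives it. Total exposures are then 1250(1 + c), of which 1250c sit in the neostigmine arm, a share of c/(1 + c).

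**4. Expected misplaced anaphylaxis cases.** These equal 1250 × c × r, with r taken from the section Sugammadex and allergy: 1 in 5000 (Japan) or 1 in 64,000 (UK).

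| Assumed c | Exposures misplaced | Share c/(1 + c) | Cases at 1 in 5000 | Cases at 1 in 64,000 |
|---|---|---|---|---|
| 2% | 25 | 2.0% | 0.005 | 0.0004 |
| 5% | 62.5 | 4.8% | 0.0125 | 0.001 |
| 10% | 125 | 9.1% | 0.025 | 0.002 |
| 20% | 250 | 16.7% | 0.05 | 0.004 |

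For comparison, the sugammadex arm itself would be expected to yield 1250/5000 = 0.25 cases, or 1250/64,000 = 0.02. The same section puts neostigmine's allergy risk close to zero, so a single misplaced case could be the whole neostigmine count.

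**5. Sensitisation, if the substudy were grouped by allocation.** Take 50 participants allocated to neostigmine, a sensitisation rate s after sugammadex of 2% to 10% (assumed), and none after neostigmine alone. Expected positives in the neostigmine group are 50 × c × s: from 50 × 0.02 × 0.02 = 0.02 to 50 × 0.20 × 0.10 = 1.0. The difference between groups becomes s − cs = s(1 − c). For example, a true 10 percentage points becomes 9.8 at c = 2% and 8.0 at c = 20%.

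**The case against.** The strongest reply is that the rule is being read too widely. Its paragraph ends by speaking only of primary analyses and only where possible. Section {20a} names randomised arms for DAH-30, pulmonary complications, mortality and QoR-15, then drops that wording for the allergy outcomes. The objectives, outcomes and sample size sections already tie allergy to the drug given, and a specific statement can be taken to override a general one. Adverse event reporting {22} assesses the causality of serious events individually, against the reference safety information for each drug. The allergy outcomes are descriptive, and the one named comparator for sensitisation is external (population sensitisation to rocuronium). Finally, a safety analysis set is commonly left to the SAP.

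Much of this stands. The text is ambiguous, and nowhere does it say outright that allergic reactions will be tabulated by allocation. The rest does not remove the point:

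- The closing sentence of the paragraph sums up the wider rule and creates no exception by receipt.
- Descriptive rates still need the right numerator and denominator.
- Causality review under {22} governs the reporting of serious events, which is separate from the outcome tables and the substudy.
- The point does not rest on an omission left to the SAP: a rule is stated, and an SAP that used drug received would depart from its literal wording.

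A reader might infer three stronger things that the documents do not support:

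- **That a crossover reaction will certainly be charged to neostigmine.** The text allows that reading but does not settle it.
- **That a planned safety contrast is biased towards no difference.** No between-arm test of allergic reactions is planned, and the exploratory regression leaves its groups undefined.
- **That earlier sugammadex exposure contaminates the single-exposure estimate.** This is a separate question from the allocation rule and rests on what a condensed article does not state. The protocol also does not say that the allergy specialist's assessment records earlier sugammadex.

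**Conclusion.** The point holds as an internal conflict to be reconciled. The broad allocation rule, taken at its word, covers two outcomes that the protocol elsewhere frames by exposure, and the optional per-protocol analysis would not repair this.

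For 2% to 20% crossover, 2.0% to 16.7% of sugammadex exposures would be counted under neostigmine. Expected misplaced anaphylaxis cases stay at or below 0.05. These figures rest on an assumed crossover range, on full receipt in the sugammadex arm, and on anaphylaxis rates. The trial's outcome is allergic reactions more broadly, for which the protocol gives no rate, so the absolute count could be larger while the share would be the same.

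The consequence is for attribution and for the exposed denominator. The sample size, the power and the primary comparison are unaffected.

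**What to change.** In {20a}, limit the allocation rule to the effectiveness outcomes. Add a sentence saying that allergic reactions within 24 hours and sensitisation findings are summarised by drug(s) actually received, in four groups: sugammadex, neostigmine, both, none. Give a table by allocation as a supplement. State that the patient groups in the exploratory regression are formed in the same way, and bring the allocation wording in the substudy follow-up section into line with the sample size section.

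The cost is small. The CONSORT diagram already requires the trial to record who did and did not receive the randomised treatment, so the work is a change of wording and one more descriptive table. The price in inference is that groups formed by receipt are not randomised. The rates should therefore be presented as descriptions of exposed patients, with the table by allocation beside them.

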## Discussion

Despite changes in surgical and anaesthetic practice, major surgery continues to be associated with unacceptably high rates of post-operative pulmonary complications. The use of neuromuscular blocking agents is consistently identified as a risk factor for PPCs, thought to be mediated by inadequate reversal of neuromuscular blockade and weakness of airway and respiratory muscles.

Patients aged over 50 years undergoing major abdominal or thoracic surgery are a large and diverse patient group at elevated baseline risk of PPCs, with a high incidence of co-morbidities such as malignancy, which are associated with additional risk. The inclusion criteria were selected with this prognostic enrichment in view.

Only two reversal agents for neuromuscular blockade are in widespread use in the UK: sugammadex and neostigmine. Sugammadex has obvious advantages, notably faster onset of action leading to more rapid return of neuromuscular function, and this has led to use in an increasing proportion of anaesthetics administered in the UK. However, its clinical effectiveness in preventing adverse patient-centred outcomes is uncertain, and the risk of future allergic reactions is unquantified. Dosing of both drugs is individualised by anaesthetists considering clinical circumstances and the results of neuromuscular monitoring which is deemed essential in national guidelines.

The primary outcome measure, DAH-30, is a composite outcome which reflects patient recovery after major surgery through length of hospital stay, readmission, and death. Lower DAH-30 is associated with age and co-morbidities, but also with the occurrence of complications, including PPCs. It is thus an ideal outcome measure for pragmatic clinical trials such as this.

A strength of the trial is the embedded observational substudy to investigate allergic sensitisation. This will be the largest of its kind to investigate potential sensitisation rates following administration of sugammadex in a routine NHS clinical setting. By combining skin testing with mast cell activation testing, the relative advantages of these techniques will be directly compared for the first time. Collectively, these data will inform our understanding of likely sensitisation rates as usage of sugammadex increases as well as the ideal allergy testing pathway for suspected sugammadex allergy.

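### The stated DAH-30 model names no prognostic covariate beyond the minimisation factors, although the protocol itself links DAH-30 to age and co-morbidities: a modest, low-cost gain in precision is available

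*Protocol article*

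**What the plan says.** In the protocol article, the section Statistical methods for primary and secondary outcomes {20a} compares the arms on DAH-30 with a count regression. Its form is to be settled once the data distributions have been seen, and it is "anticipated to be zero-inflated Poisson regression model or zero-inflated negative binomial regression model". On covariates the section says: "The model will include minimisation variables (hospital site, emergency vs elective surgery, thoracic vs abdominal surgery". The logistic models for post-operative pulmonary complications (PPCs) and mortality, which supplement chi-squared tests, adjust for the same factors. No other covariate is named for any of these models.

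The Discussion says of the primary outcome: "Lower DAH-30 is associated with age and co-morbidities, but also with the occurrence of complications, including PPCs". Neither age nor co-morbidity is among the minimisation factors listed under Sequence generation {16a}.

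Age is recorded for every participant, because Eligibility criteria {10} sets a minimum of 50 years. Baseline data are collected before surgery (Table 1), but the article does not list the individual items.

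The Sample size section {14} uses an unadjusted comparison of two means and takes no credit for covariates. It claims that "the randomisation of 2500 participants will allow detection of a one-day difference in DAH-30 between trial arms". The inputs behind that claim are an SD of 7.5, a two-sided 5% level, 90% power and an allowance of 5% for attrition.

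**The concern.** The protocol identifies patient characteristics that it regards as related to its primary outcome, and the stated model for that outcome does not name them. The population is wide: there is no upper age limit, and both elective and emergency surgery are eligible. Some of the spread in DAH-30 is therefore plausibly explained by age and co-morbidity within the strata that the model already uses.

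The stake is precision, with some protection against chance imbalance on factors that minimisation does not control. Prognostic covariates measured before randomisation would be expected to narrow the confidence interval for the treatment effect without biasing it.

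Timing matters as well. The trial is open-label and the model form is to be chosen after looking at the data distributions. A covariate added at that stage would be open to challenge; one named beforehand would not.

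**Working it through.** **Inputs from the Sample size section {14}.** Total 2500, or 1250 per arm; target difference 1 day; SD 7.5 (the source data gave a "mean DAH-30 of 22.4 days (SD 7.4"); two-sided 5%; 90% power; 5% loss.

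**Input not in the documents.** R², the further share of DAH-30 variance explained by age and co-morbidity. It is assumed here to lie between 2% and 15%.

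**Step 1: reproduce the stated size.**
- n per arm = 2 × (1.96 + 1.2816)² × 7.5² / 1² = 1182.1, rounded up to 1183. The total is 2366.
- With 5% loss: 2366 / 0.95 = 2491, against the stated 2500.
- Analysed per arm at 2500: 1250 × 0.95 = 1187.5. The standard error is 7.5 × √(2/1187.5) = 0.308 days.
- Power = Φ(1/0.308 − 1.96) = 90.1%.

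The stated figure reproduces with no covariate adjustment at all.

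**Step 2: effect of further covariates, linear approximation.** Replace 7.5 by 7.5 × √(1 − R²) and keep 1187.5 per arm. The 95% CI half-width is 1.96 × SD × √(2/1187.5). The last column is the total needed for 90% power, including 5% loss.

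| Assumed R² | Adjusted SD | Power for 1 day | 95% CI half-width (days) | Narrowing | Total needed |
|---|---|---|---|---|---|
| 0 | 7.500 | 90.1% | 0.603 | none | 2491 |
| 2% | 7.425 | 90.7% | 0.597 | 1% | 2440 |
| 5% | 7.310 | 91.5% | 0.588 | 2% | 2365 |
| 10% | 7.115 | 92.9% | 0.572 | 5% | 2240 |
| 15% | 6.915 | 94.1% | 0.556 | 8% | 2116 |

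**Step 3: the starting point.** The first row treats the full SD of 7.5 as unexplained, but the planned model already contains site, urgency and surgery type. Suppose, for illustration, that these explain 10% of variance. Power then starts at 92.9%, and a further 5% of total variance takes it to 94.1%. That is a gain of 1.2 points, against 1.4 points (90.1% to 91.5%) when starting from zero. The table therefore somewhat overstates the points of power left to gain.

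**Step 4: chance imbalance.** With 1187.5 per arm, the standardised difference in mean age between arms has a standard error of about √(2/1187.5) = 0.041 SD. About 95% of allocations would fall within 1.96 × 0.041 = 0.08 SD. A material imbalance is unlikely, so precision is the main reason for the change.

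**The case against.** The strongest case against is that this is a matter for the analysis plan. The article condenses a longer protocol, the statistical analysis plan is not shown, and either could name further covariates. The text says what the model will include; it does not exclude anything. A reader might infer that age and co-morbidity have been ruled out of the primary model, and the wording does not support that. What stands on the text is narrower: a covariate set is stated, and no prognostic variable beyond the minimisation factors is in it.

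Other objections stand in part:

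- **Strength of association.** A reader might take the Discussion to mean that age and co-morbidity largely determine DAH-30. It reports an association and gives no strength, so the size of the gain cannot be fixed from the documents.
- **Model.** The 1 − R² reduction is a linear-model result. In a zero-inflated Poisson or negative binomial model, covariates may enter both parts, the gain is not guaranteed, and a conditional effect need not equal the difference in mean days used for the sample size. It would be too strong to call the precision free.
- **Co-morbidity data.** No section shows that a co-morbidity or physical-status score is collected. Only age is certain to be available.
- **Importance.** The gain is a few points on power that is already adequate.

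These objections limit the size and wording of the point. None shows that adjusting for age would be wrong or costly.

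**Conclusion.** The point holds as a minor recommendation. The stated DAH-30 model names no prognostic covariate beyond the minimisation factors, while the same document reports that age and co-morbidities are associated with the outcome. Naming at least age would be expected to improve precision.

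A reader might go further and infer that the primary analysis is invalid, that the trial is underpowered, or that the methods and the Discussion contradict each other. None of these follows. Adjusting for the factors used in minimisation is appropriate, the randomised comparison is valid without more covariates, the stated 90% power reproduces without adjustment, and the Discussion promises no adjustment for age.

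On an assumed further 2% to 15% of variance explained, power for one day moves from about 90% to about 91% to 94%, and the confidence interval narrows by about 1% to 8%. These figures rest on that assumed range, on a linear approximation, and on a baseline that ignores variance already explained by the minimisation factors. If the covariates have no predictive value there is no gain, and at this sample size the loss is negligible.

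**What to change.** Before outcome data by arm are examined:

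1. Name age as a covariate in the primary DAH-30 model and in the adjusted PPC and mortality models, alongside the three minimisation factors. Enter it as continuous with a form that allows non-linearity, such as a spline. For the zero-inflated model, state which part or parts it enters.
2. If the trial records a co-morbidity or physical-status measure before randomisation, name it too, with simple imputation of missing baseline values so that no participant is dropped for a covariate.
3. Report the treatment effect on DAH-30 as a standardised (marginal) difference in mean days with its confidence interval, so that the result is on the scale of the one-day target.

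If the analysis plan already does this, no change is needed beyond making the two documents agree.

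The cost is a few lines of text, slightly more modelling work, and the handling of any missing baseline values. Age needs no new data collection. Whether a co-morbidity measure is available has to be checked against the case report form.
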